### Sample size

Based on two studies using the antisaccade task in clinical samples, we calculated two a-priori power analyses using G*Power 3.1 [25] for ANOVAs (Analyses of Variance) to detect large effect sizes (Cohen´s *f* = .40, *α* = .05, power = .85) in our primary outcome (i.e. antisaccade latencies) at baseline (aim 1) [12] and for the training effect (aim 2) [21]. Results indicated a required total sample size of 59 participants (30 per group).

### Procedure

#### Overall procedure

After an initial telephone screening, eligible participants are invited to provide written informed consent and participate in a clinical interview via telephone. If they fulfill eligibility criteria, they are invited to a laboratory appointment at the University of Siegen and asked to fill in an online battery of questionnaires beforehand via LimeSurvey 3.28.18 [26]. A schedule of enrollment, intervention and assessment can be found in Fig 1.

**Fig 1 pone.0292471.g001:**
[figure not shown]
Schedule of enrollment, intervention, and assessment. *Note*. Assessment schedule, including all outcome measures. An X in the corresponding box indicates that assessment takes place at a certain time point. BAT: Behavioral Avoidance Test. MINI: Mini International Neuropsychiatric Interview [24]. SPQ: Spider Phobia Questionnaire [23]. BIS: Behavioral Inhibition System [27]. BAS: Behavioral Approach System [27]. NEO-FFI: NEO Five-Factor Inventory [28]. STAI: State-Trait-Anxiety-Inventory [29]. FEAS: Questionnaire on Disgust and Fear of Spiders [30]. ABI: inventory of coping with anxiety [31]. CERQ: Cognitive Emotion Regulation Questionnaire [32]. PANAS: Positive and Negative Affect Schedule [33]. UI-18: Intolerance of Uncertainty [34]. ASI-3: Anxiety Sensitivity Index [35]. NISS: Need Inventory of Sensation Seeking [36]. RSES: Rosenberg Self-Esteem Scale [37]. ANPS: Affective Neuroscience Personality Scales [38]. SEE: Scales for experiencing emotions [39]. MWT-B: Multiple-Choice Vocabulary Intelligence Test [40]. FEE: Disgust Responsiveness [41].

The laboratory appointment begins with a baseline assessment, including a behavioral avoidance test (BAT), a free-viewing task, and the antisaccade task (all of which are described below). This part of the study corresponds to aim 1 (see *background* and Fig 2). Then, participants complete the antisaccade training or the control condition (prosaccade training), according to a randomization scheme. After training, the antisaccade task and the BAT are repeated (post-1-assessment), and the study ends for the HCs. This part of the study corresponds to aim 2 (see *background* and Fig 2). Patients with SP then complete a second training. Here, participants switch training conditions. After the second training, the antisaccade task, the free-viewing task, the BAT, and the SPQ is repeated (post-2-assessment). This part of the study corresponds to aim 3 (see *background* and Fig 2).

**Fig 2 pone.0292471.g002:**
[figure not shown]
The consort flow diagram. *Note*. BAT: Behavioral avoidance test. HC: Healthy control participants. n: Number of participants. SP: Participants with spider phobia. SPQ: Spider phobia questionnaire. Key assessments to address aim 1 are shaded in green (baseline-assessment). Additionally, the intervention (antisaccade and prosaccade training) and the post-1-assessment are relevant for aim 2 (i.e., areas shaded in green and blue). In addition to assessments targeting aim 1 and 2, a second intervention and the post-2-assessments is relevant for aim 3 (i.e., areas shaded in green, blue and yellow). Note: Aim 3 refers to participants with spider phobia only.

#### Laboratory assessments

*Antisaccade task*. In the antisaccade task, ten stimuli, created and used by Kolassa and colleagues in previous studies [42], are presented. Stimulus materials comprise five phobia-related pictures (black schematic pictures of spiders) and five neutral pictures (black schematic pictures of flowers), as depicted in Fig 3, to assess the stimulus-dependency of predicted differences in inhibitory control functions.

**Fig 3 pone.0292471.g003:**
[figure not shown]
Overview of tasks and intervention. *Note*. A: Antisaccade task, employs stimuli from Kolassa and colleagues [42]. B: Free-viewing task, uses phobia-related stimuli from *Geneva Affective Picture Database* (GAPED) [43]. C: Antisaccade training, uses additional phobia-related stimuli from GAPED. Arrows show the instructed viewing direction of the participants. D: Prosaccade training, uses neutral stimuli from GAPED. Arrows show the instructed viewing direction of the participants. ITI: Inter-Trial-Interval. s: Seconds.

The antisaccade task is conducted at baseline, post-1- and post-2-assessment. For each assessment, participants are placed in a darkened room. Eye movements are recorded via Eye-Link 1000 plus (SR Research Ltd., Canada) at a sampling rate of 1000 Hz. For each trial, a black fixation dot (0.25° x 0.25°) is presented on a white screen, with 84 cm distance to the participant, for a period of 1.5–3.5 seconds. After the fixation period, the dot vanishes, and the visual stimulus is immediately presented (so-called step-paradigm). The visual stimulus (3° x 2.25°) is randomly presented at 12° to the left or right of the visual field for one second.

Phobia-related and neutral stimuli are presented equally often in a randomized order. At baseline, the task includes five blocks as proposed by Antoniades and colleagues [44]: three antisaccade blocks (each including 40 antisaccades, i.e. 20 antisaccades to phobia-related and 20 antisaccades to neutral stimuli, each stimuli are shown 4 times), as well as two prosaccade blocks (each including 60 prosaccades, i.e. 30 prosaccades to phobia-related and 30 prosaccades to neutral stimuli, each stimuli are shown 6 times), one preceding and one following the antisaccade blocks. Antisaccade tasks at post-1- and post-2-assessment include only three blocks of antisaccades (each including 40 antisaccades), as prosaccades are already assessed at baseline, expenses for participants should be reduced and outcomes are only related to antisaccade performance. Each block is followed by a one-minute break.

Assessment of antisaccade performance are relevant for aims 1–3 of the study.

### Free-viewing task and valence and arousal rating

In the free-viewing task, 24 pictures of the *Geneva Affective Picture Database (GAPED)* [43] are presented. The selected stimulus material comprises eight neutral pictures (inanimate objects), eight generally aversive but phobia-unrelated pictures (animal mistreatment), and eight phobia-related pictures (naturalistic spiders), respectively. Pictures are presented in two blocks of trials, each block depicting all of the 24 pictures in a randomized order. Via ratings provided by the authors of the database [43], negative pictures and pictures of spiders were matched regarding valence (negative: *M* = 21.35, *SD* = 8.78; spider: *M* = 20.46, *SD* = 7.77, *t*(15) = 1.00, *p* = .83) and arousal (negative: *M* = 66.30, *SD* = 5.18; spider: *M* = 66.99, *SD* = 6.41, *t*(15) = 1.02, *p* = .84), while neutral pictures had more positive valence ratings (*M* = 50.54, *SD* = 1.65) and lower arousal ratings (*M* = 21.77, *SD* = 6.01). Pictures are presented for six seconds each, followed by a twelve-second inter-trial-interval, as depicted in Fig 3.

While the pictures are presented, psychophysiological measures are assessed. To assess participants’ startle response, an acoustic stimulus (white noise, 50 ms, 105 dB(A), instantaneous rise time) is presented via headphones. This stimulus is presented 18 times during visual stimulus presentation for each block, that is six times per visual stimulus category, in a randomized order. The startle-eliciting stimulus occurs randomly between 4 and 5.5 seconds after visual stimulus onset. During inter-trial intervals, startle responses are elicited 6 times per block in a randomized order between 7.5 and 9.5 seconds after inter-trial-interval onset. Before each block, the startle-eliciting stimulus is presented 6 (first block) or 3 times (second block), respectively, to ensure initial habituation. Startle magnitude is measured by activity of the musculus orbicularis oculi (unilateral) via electromyography (EMG), utilizing a Biopac MP160 system (Biopac Systems, Inc., USA) with H124SG electrodes (Kendall). Design of startle assessment closely follows established methods [45]. Heart rate is derived from continuously recorded electrocardiogram (ECG) utilizing a Biopac MP160 system with EL503 electrodes (Biopac). To assess skin conductance responses, electrodermal activity [46, 47] is measured utilizing a Biopac MP160 system with EL507 electrodes (Biopac) at the thenar/hypothenar of the non-dominant hand.

Psychophysiological measures are assessed in the free-viewing task at baseline and post-2-assessment and are relevant to address aims 1 and 3 of the study.

Directly after the free-viewing task, each picture is presented again, and participants are asked to rate each picture in terms of valence and arousal on a visual analog scale. Pictures and the sequence of the valence and arousal ratings are randomized between participants. Ratings are used to describe stimulus-characteristics based on the study sample.

### Behavioral Avoidance Test (BAT)

Avoidance behavior is assessed by an in vivo BAT. Behavioral avoidance is indexed by the final distance (in cm) between the participant and a real spider (brachypelma auratum). For a detailed description, also see [48]. BAT is conducted at baseline, post-1- and post-2-assessment and is relevant to address aims 1 and 3 of the study.

#### Intervention

*Experimental condition (antisaccade training)*. The intervention in this trial consists of an antisaccade training. Participants must look at the center of a screen. As depicted in Fig 3, stimuli are presented for one second left or right in the peripheral field of vision with a visual angle of 12°, after a fixation period of 1–3.5 seconds, based on recommendations by Antoniades and colleagues [44]. Participants are instructed to look at the mirrored position on the screen. Stimuli constitute ten (additional) spider stimuli from the *GAPED* [43], which are shown in random order. We opted for phobia-related stimuli because the training of inhibitory control is expected to be maximal in this condition. The training includes two blocks with 80 antisaccades each, separated by a pause of one minute. Adherence to interventions is supported by carefully instructing participants before each training block. Implementation of the described training (including the control condition described below) is relevant to address aims 2 and 3 of the study.

### Control condition (prosaccade training)

To examine the effect of antisaccade training on antisaccade performance, we compare the effects of the antisaccade training with the effects of a prosaccade training on antisaccade performance. The prosaccade training is employed to control for potential fatigue effects caused by voluntary eye movements in general rather than antisaccades specifically.

In the control condition, as depicted in Fig 3, participants are instructed to look at stimuli that appear left or right in the periphery field of vision for one second after a fixation period of 1–3.5 seconds. Ten neutral stimuli from the *GAPED* [43] are used. In the control condition, we employ neutral stimuli rather than the phobia-related stimuli employed in the antisaccade training to prevent potentially beneficial effects of perceptual exposure on antisaccade performance. The training includes two blocks with 80 prosaccades each, separated by a pause of 60 seconds.

### Ethics approval

The study protocol was approved by the local Ethics Committee of the University of Siegen (07/2021), Germany (reference number: ER_39_2021). The study was designed in accordance with the Declaration of Helsinki, Good Clinical Practice guidelines, and the SPIRIT reporting guidelines. During the run of the study, ethical, legal, and social aspects are anticipated and addressed. Participants provide written informed consent to the experimental procedure before inclusion in the study. Informed consent is obtained by research assistants conducting the interviews for eligibility. Participation is entirely voluntary, and participants have the right to withdraw their consent at any time. Participant information is pseudonymized and stored on a secure database and can only be accessed by the involved researchers and research assistants.

### Randomization and blinding

The randomization scheme was implemented utilizing block randomization. Participants are randomized via sequential numbers provided in a separate document.

Though participants are not especially informed about their allocation to a certain condition, they might have been aware of the condition. A blinding of investigators is not possible.

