### Analysis

#### Preprocessing

*Eye tracking*. To detect saccadic eye movements, conservative thresholds are used. Saccades are defined as eye movements with a velocity > 35°/sec, an acceleration > 9500°/sec^2^ and an amplitude > 3°. For the trial to be classified as valid, onset latency of the first saccadic eye movement after stimulus onset must be greater than 70 ms. Starting coordinates of the eye movement must fall within a square of 5° x 5° around the fixation stimulus. Additionally, blinks must be absent. Trials with no recorded eye movements after stimulus onset are also classified as invalid. A correct antisaccade (secondary outcome) is defined as a valid saccade in the opposite direction of the peripheral visual stimulus. Antisaccade latency (primary outcome) is defined as the time difference between stimulus onset and initiation of the correct antisaccade. Participants are excluded from analysis if > 50% of maximal possible trials are invalid.

*Psychophysiological data*. ECG data is pre-processed using the PhysioData Toolbox (Version 0.6.3) [49]. The signal is filtered using a bandpass filter with a low cut-off at 1 Hz and a high cut-off at 50 Hz. From the ECG signal, R-peaks are retrieved, which serve to calculate heart rate measures. The ECG signal are visually inspected for artifacts, as well as erroneous or missed R-peaks. Missed R-peaks are added manually, erroneous R-peaks are deleted. Trials with artifacts in the ECG signal are discarded.

Skin conductance data is pre-processed using the PhysioData Toolbox. The raw signal is filtered and resampled to a 20 Hz time-vector spanning the length of the filtered signal, using spline interpolation. By first applying a moving minimum filter, followed by smoothing the result applying a Gaussian kernel, the tonic component is calculated. The phasic component is calculated by applying a 1st order high pass Butterworth filter of 0.5 Hz. The signal is visually inspected for artifacts. Trials with artifacts in the SCL signal are discarded.

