The raw EMG signal is filtered using a band-pass filter ranging from 10 to 500 Hz, as well as rectified and smoothed, using a low-pass resistor-capacitor filter, utilizing a time constant of 10 ms. A C++-based software tool is used to identify peak responses in the rectified and integrated EMG signal. Additionally, the signal is visually inspected for artifacts (e.g., preceding blinks immediately before the startle probe), as well as erroneously detected response peaks. Trials with artifacts in the EMG signal are discarded, erroneously detected response peaks are corrected manually. Startle response amplitude is defined as the difference between EMG peak and baseline amplitude in a 200 ms response window.

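### The blanket statement that investigators cannot be blinded is too broad: visual review and manual correction of ECG, skin-conductance and startle recordings can be masked

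*Protocol article*

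**What the plan says.** On blinding, the protocol article (*Randomization and blinding*) makes two statements. On participants: "Though participants are not especially informed about their allocation to a certain condition, they might have been aware of the condition". On staff: "A blinding of investigators is not possible". It does not separate those who run the session from those who later process the recordings.

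*Preprocessing* then describes steps that depend on an operator's eye:

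- **ECG:** "The ECG signal are visually inspected for artifacts, as well as erroneous or missed R-peaks". Then: "Missed R-peaks are added manually, erroneous R-peaks are deleted". Trials with artifacts are dropped.
- **Skin conductance:** "The signal is visually inspected for artifacts. Trials with artifacts in the SCL signal are discarded". No manual change of values is described.
- **Startle EMG:** after software peak detection and visual inspection, "Trials with artifacts in the EMG signal are discarded, erroneously detected response peaks are corrected manually".

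No section says that these steps are masked. *Ethics approval* states: "Participant information is pseudonymized".

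According to *Free-viewing task and valence and arousal rating*, these signals are recorded at baseline and post-2 and serve aims 1 and 3.

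**The concern.** Keeping or dropping a trial, or moving a detected peak, is a judgement that sets the value of the outcome. If the person judging knows which assessment or picture type a trial belongs to, or how well that participant did on the antisaccade task, the judgement can lean towards the expected result. The article declares blinding impossible across the board, so a reader must assume that no protection is intended at this stage, although a simple one is available.

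At stake are the links between antisaccade performance and physiological fear responses in aim 1, and between their changes in aim 3. The article presents these links as the bridge from a laboratory measure to clinical relevance.

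**Working it through.** The plan gives no figure on this point. Its one design figure, a total sample size of 59, concerns antisaccade latency. It reproduces with a noncentral F, numerator df 1, noncentrality 0.40² × 59 = 9.44 and α = .05: power is 0.856 against the stated .85. Masking the signal review would change none of these inputs. The check is therefore mainly a reading of sections side by side.

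**1. Which steps are discretionary?** The eye-tracking rules are numeric: velocity above 35°/s, acceleration above 9500°/s², amplitude above 3°, latency above 70 ms, and a start within a 5° × 5° square. No manual step is described, so latency and error rate are not exposed. For ECG and skin conductance no artifact threshold is given. For EMG there is only an example, blinks just before the probe.

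**2. How many decisions are there?** Startle has 18 picture probes and 6 interval probes per block, over two blocks: (18 + 6) × 2 = 48 per assessment, not counting the habituation probes. Six picture probes per category and block give 6 × 2 = 12 with spider pictures. If the index is a mean over spider pictures (assumed; the article does not define it), one discarded trial removes 1/12, about 8%, of its data.

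**3. Where do the measures enter the analysis?** Under *Statistical analyses*, physiology appears twice: in multiple regressions within patients with spider phobia (aim 1, antisaccade latency or error rate as the dependent variable) and in change associations within the same patients (aim 3, baseline to post-2). The group-by-stimulus models use antisaccade latency and error rate. The sequence-by-time models use latency, error rate and avoidance distance.

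**4. What kind of editing would bias these associations?** Let X be the true physiological value, e the effect of editing, X* = X + e the scored value, and Y the antisaccade result. With a single predictor, the slope of Y on X* is

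[cov(X, Y) + cov(e, Y)] / var(X + e).

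- If e is the same for everyone, cov(e, Y) = 0 and the variance is unchanged. The slope is not biased.
- If e varies but is unrelated to X and Y, the slope shrinks towards zero.
- If e tracks Y, cov(e, Y) is not zero and the association is biased directly.
- If e depends on the response itself, for example when large responses to spider pictures at post-2 are more readily called artifacts, both covariance and variance change.

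For aim 3 the same holds with X, e and Y replaced by their changes. The harmful routes need knowledge of the antisaccade result, the time point or the picture category.

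**5. Which labels matter?** Random IDs unlinked from the eye-tracking results close the most direct route. Hiding time point and picture category limits the last one. Diagnosis is constant within the planned analyses, but it is cheap to hide, and a visible post-2 label would reveal it, because only patients have that assessment. Training order matters little: by post-2 both sequences have had both trainings.

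**The case against.** The strongest reply has three parts.

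- **Scope.** The sentence stands in a section about allocation and is true of session staff. The article never says who reviews the signals or what they can see, and scorer masking is a detail that may stand in a fuller document. It is right that the scorers and their knowledge are unknown. But the article is not merely silent: it makes an unqualified statement that its own processing steps show to be too broad.
- **Mechanism.** A uniform shift in scored physiology leaves a regression slope or correlation unchanged. This stands, and it narrows the concern to edits that vary between participants.
- **Weight.** The primary and secondary outcomes are rule-scored, and aim 3 is exploratory. This also stands.

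A reader might go further and infer that unmasked editing inflates a patient-versus-control or spider-versus-neutral test of physiology. With 30 per group and an assumed bias of 0.2 SD, the noncentrality is 0.2 × √15 = 0.775, and a two-sided 5% t-test would reject in about 11.9% of cases (6.7% at 0.1 SD, 20.8% at 0.3 SD). The arithmetic is sound, but *Statistical analyses* describes no such test, and the bias values have no source in the document. The abstract's wording of aim 1 could suggest that associations are contrasted between groups, but the analysis section confines the regressions to patients.

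Three other inferences also go too far. Skin-conductance values are not edited by hand; trials are only rejected. Nothing says raw recordings are destroyed, so masked re-scoring could still reveal or repair a bias. And masking is not entirely free, since trial labels may sit inside the files.

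**Conclusion.** The concern holds in limited form. The statement on investigator blinding should not extend to the visual review and manual correction of ECG, skin-conductance and EMG recordings. What is exposed is the set of within-patient associations in aim 1 and the exploratory change associations in aim 3. The main antisaccade comparisons are not exposed. No size of bias can be derived from the document, and none is claimed.

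The conclusion rests on two assumptions: that the review takes place after recording, which the description as preprocessing with software tools implies but does not state, and that scorers are not already masked. If they are, one sentence saying so settles the matter, though the blanket sentence would still need to be narrowed. Pseudonymization alone does not settle it, because a pseudonym need not hide time point or picture category, or break the link to the antisaccade data.

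**What to change.** In *Randomization and blinding*, limit the sentence to the conduct of sessions. Add there or under *Preprocessing*, for example: Visual inspection and manual correction of ECG, skin-conductance and EMG recordings are carried out on files recoded with random IDs and unlinked from antisaccade results. Diagnosis, assessment time point and, where the file format allows, picture category are hidden from the scorer. The key is opened only after the edited data are locked.

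Masking of training order can be included but adds little.

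The cost is a small recoding effort, including trial labels stored inside the recordings, and a short change of text. The same scorers can do the work. Sample size, significance level, procedures and participant burden do not change. If some recordings have already been reviewed unmasked, the plan should say so; re-scoring them masked would be the remedy if the raw files are kept.
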